#### Secondary outcome measures

Secondary outcome measures will include assessing ulcer pain, quality of life and economic evaluation.

Ulcer pain will be measured weekly using a 100 mm Visual Analogue Scale (VAS). Pain will be assessed prior to, during and following each treatment. The far left end of the scale (0 mm) will be labelled as no pain and the far right end of the scale (100 mm) will be labelled as worst pain imaginable. The VAS has been widely used and has been shown to be a valid and reliable pain assessment tool [34].

A health-related quality of life tool will be used to gain perspective from each participant. This will be undertaken at the initial treatment, at three months and again at six months. If an ulcer heals prior to the end of the six month study period the tool will be applied at that point. The Eq 5D-5 L [35] assessment tool analyses five health-related quality of life domains including mobility, self-care, usual activities, pain/discomfort and anxiety/depression. This tool has been widely used and has been validated for use in patient groups with diabetes [36].

All data for the secondary outcome measures will be collected by the treating podiatrist. No blinding will occur for this data.

Each outcome measure and their time points of collection are summarised in Table 4.

**Table 4 T4:** Outcome measures and timeframes

** *Data collection* **	** *Measurement tool* **	** *Data collected method* **	** *Timeframe* **
*Measurement of total ulcer area*	*Centimetres squared;*	*Research assistant*	*Weekly: Post-treatment until healed or at 6 months*
	*Tracing from photographs and counting squares*		
*Measurement of ulcer depth*	*Centimetres;*	*Treating podiatrist*	*Weekly: post-treatment until healed or at 6 months*
	*Using sterile probe*		
*Ulcer pain*	*Visual analogue pain scale 100 mm*	*Treating podiatrist*	*Weekly: Pre-treatment, during treatment, post-treatment until healed or 6 months*
*Quality of life*	*EQ-5D-5 L tool*	*Participant questionnaire*	*Initial treatment, at 3 months, at 6 months*

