## Introduction

### Background

Diabetes is rapidly increasing in global prevalence, morbidity and mortality. In 2011, 366 million people globally were living with diabetes, a figure that is equivalent to 8.3% of the world’s adult population. It was estimated the international community would not reach this figure until 2030 [1].

In Australia the prevalence of type 2 diabetes has increased over the past two decades and continues to rise. Approximately 7% of the Australian population is thought to have type 2 diabetes and it is estimated that 15% of people with diabetes will develop a foot ulcer during their lifetime [2]. The consequences of having diabetes in Australia are significant with over 500,000 hospital admissions and 12,000 deaths attributed to the condition in 2004 alone [1].

The pathophysiology of foot ulceration is complex and usually multi-factorial. Peripheral sensory neuropathy, foot deformity and external trauma, when occurring concurrently, have been identified as being the three most common factors that predispose to diabetes-related foot ulcers (DRFU) [3]. Peripheral arterial disease has also been shown to lead to the development of ischaemic and neuro-ischaemic DRFU [2]. Regardless of the true aetiology, the same complications can arise with all DRFU, including soft tissue infection, osteomyelitis, tissue necrosis and failure of ulcer healing, all of which may require hospital admission and potentially result in amputation [4].

Diabetes has been acknowledged to be the most common cause of non-traumatic lower-limb amputation in Australia [5]. Furthermore, acute complications affecting foot ulceration have been reported as the leading cause of diabetes-related hospital admissions and amputation [4]. For the years 2004–2005 the Australian Institute of Health and Welfare reported that DRFU resulted in 9900 acute hospital admissions [4]. In the same period 3400 diabetes-related lower limb amputations were also reported [2].

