It is hypothesised that use of LFUD in the treatment of DRFU would improve healing rates when compared with NSSD. There will be four aims within this study. The primary aim is to determine if there is a difference in healing rates for DRFU, using NSSD compared to LFUD. Secondary aims include assessing for differences in pain during and post-treatment, determining if there is a difference between the quality of life of participants who have an ulcer undergoing either method of debridement and if there is a difference in overall costs between NSSD and LFUD.

This clinical trial will provide important information in the field of ulcer management; provide a better understanding of the efficacy of NSSD and the newer technology of LFUD. It will also provide health services with a better understanding of the financial impacts of both treatments. This protocol has been designed and reported to ensure it corresponds to the 33 items of the Standard Protocol Items: Recommendations for Interventional Trials (SPIRIT) checklist [26].

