### Participants and setting

Patients with diabetes and a foot ulcer/s, who are referred to and treated by the Podiatry Department at Monash Health, will be invited to participate in this study. Patients may be inpatients and receiving podiatry care on the ward or outpatients referred by the patient’s primary medical care team.

This study is a single centre trial. The average length of stay for an acute hospital admission in Australia is 6 days [27]. Participants may be recruited during their hospital admission but it is anticipated they will receive treatment primarily in the outpatient setting. Inpatients, however, can receive either treatment if they meet inclusion criteria for this study as both study interventions can be undertaken by the bedside as well as in an outpatient clinical setting.

A standard initial podiatric assessment will occur at baseline including a neurovascular assessment, medical and surgical history, medications history, diabetes management and control history including glycated haemoglobin (Hba1c), footwear assessment, ulcer aetiology, ulcer duration and previous management. If the participant meets the inclusion criteria (Table 1) as determined by the treating podiatrist, the patient will be informed about the research project and written consent will be obtained to participate in the study.

**Table 1 T1:** Participant inclusion and exclusion criteria

**Inclusion criteria**	**Exclusion criteria**
** *General:* **	** *General:* **
≥ 30 years of age	Patients taking immunosuppressive medications
Able to provide informed consent	Known allergy to ulcer dressing products
Ulcers present for greater than 1 month	Pre-existing ulcer pain preventing either type of debridement
Ulcers ≥ 1 cm^2^	
** *Vascular:* **	** *Vascular:* **
Palpable pedal pulses OR biphasic or triphasic pedal pulses on doppler OR toe pressure ≥ 45 mmHg	Non-palpable pedal pulses OR monophasic pedal pulses on Doppler OR toe pressure ≤ 45 mmHg
** *Ulcer classification:* **	** *Ulcer Classification:* **
Infected ulcers being appropriately managed	Dry gangrenous ulcer
** *Those meeting The University of Texas Wound classification criteria * **[28]** *:* **	Fungating ulcers
*A1, A2, A3 (wounds of varying depth without infection or ischaemia)*	Malignant ulcers
*B1, B2, B3 (wounds of varying depth with infection only)*	** *Those meeting the University of Texas wound classification criteria * **[28]** *:* **

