### Interventions

The two interventions are the two different methods of ulcer debridement, LFUD and NSSD. The techniques for both treatments are as described in Table 2.

**Table 2 T2:** Standard step-by-step technique for LFUD and NSSD

**LFUD**	**NSSD**
1) Constantly move the handpiece to prevent ultrasound burning tissue	1) Start debriding at the distal most aspect of the ulcer
2) Start debriding at the distal most aspect of the ulcer	2) Moving scalpel proximally with each motion
3) Moving the handpiece left to right and from the distal to proximal aspect of the ulcer	3) Once the distal to proximal ulcer has been debrided then debride from left side to right side
4) Once the entire ulcer surface has been debrided re-commence the same technique from the distal most aspect of the ulcer	4) Continue until as much necrotic tissue has been removed as possible
	5) Any peri-wound tissue that requires removal (i.e. callus, maceration) will occur using a scalpel.
5) Continue until as much necrotic tissue has be removed as possible	
6) Any peri-wound tissue that requires removal (i.e. callus, maceration) will occur using a scalpel. The wound base will not be debrided with the scalpel.	

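### The covariates fixed for all analyses were chosen for healing and omit baseline sensation and baseline pain, so a null pain result could partly be a floor effect

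*Protocol article*

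**What the plan says.** Pain is one of the article's stated aims. The Background section says: "Secondary aims include assessing for differences in pain during and post-treatment". Under Secondary outcome measures, pain is scored weekly on a 100 mm VAS whose lower end, 0 mm, means no pain, and "Pain will be assessed prior to, during and following each treatment". The treating podiatrist collects it unblinded.

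The Statistical analysis section describes models for healing and for ulcer size. It then names two adjustment variables for all analyses: infection of the wound at baseline and baseline HbA1c. The reason given for each is that it delays healing. No pain model is described.

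Four other places bear on the point:
- **Background:** "Peripheral sensory neuropathy, foot deformity and external trauma, when occurring concurrently, have been identified as being the three most common factors" that predispose to these ulcers. Arterial disease is described as a further cause.
- **Table 1:** inclusion requires "Palpable pedal pulses OR biphasic or triphasic pedal pulses on doppler OR toe pressure ≥ 45 mmHg". The University of Texas classes with ischaemia (C and D) are excluded, and so is "Pre-existing ulcer pain preventing either type of debridement".
- **Participants and setting:** "A standard initial podiatric assessment will occur at baseline including a neurovascular assessment".
- **Table 2:** the ultrasonic (LFUD) technique ends with "Any peri-wound tissue that requires removal (i.e. callus, maceration) will occur using a scalpel. The wound base will not be debrided with the scalpel". The sharps (NSSD) technique has the same peri-wound scalpel step.

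**The concern.** Adjustment helps when the covariate predicts the outcome. Infection and HbA1c were picked because they bear on healing. What a patient reports on a pain scale during debridement is likely to depend more on whether the foot can feel, and on how painful the ulcer was at the start. Both are recorded, but neither is in the stated adjustment set.

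The scale also has a hard lower bound. A participant with little sensation may score near 0 mm whichever instrument is used, and such participants dilute any real difference among those who can feel the procedure. The eligibility criteria remove ischaemic ulcers and the most painful ones, which may leave more participants with reduced sensation. If so, a finding of no difference in pain would say little about patients with sensation, and a reader could mistake it for equal tolerability.

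**Working it through.** **1. The plan's own figures.** The article gives no SD, target difference or power for pain. Its only sample size is for healing. With 0.25 against 0.41, two-sided alpha 0.05 and 80% power, the continuity-corrected formula gives 147 ulcers per group, as stated. The design effect is 1 + (3 − 1) × 0.05 = 1.10. Then 147 × 1.10 = 161.7 (stated as 161), and 161.7 / 3 = 53.9, so 54 participants per group. This reproduces, but only the 54 is used below.

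**2. Covariates against outcome.**

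| Baseline item | Recorded? | In the stated adjustment set? | Reason given |
|---|---|---|---|
| Infection | yes | yes | delays healing |
| HbA1c | yes | yes | delays healing |
| Sensory status | yes, within the neurovascular assessment; test not named | no | – |
| First pre-treatment VAS | yes | no | – |

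**3. Dilution, on assumed values.** Suppose the arms differ by 15 mm in feet with sensation and by 0 mm in feet without. Then pooled difference = sensate share × 15 mm:
- 20% sensate: 0.20 × 15 = 3 mm
- 30% sensate: 0.30 × 15 = 4.5 mm
- 60% sensate: 0.60 × 15 = 9 mm

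**4. Power, on a second set of assumed values.** Take 54 per arm, one score per participant, sensate means of 30 and 20 mm with SD 18.5 mm (chosen to give about 80% power when all are sensate), and insensate scores of 0 in both arms. With sensate share p, each arm has mean m = pμ and variance p(18.5² + μ²) − m². The SE is √[(v₁ + v₂)/54], and power is Φ(difference/SE − 1.96). At p = 0.5, v₁ = 0.5 × (342.25 + 900) − 15² = 396.1 and v₂ = 0.5 × (342.25 + 400) − 10² = 271.1. So SE = √(667.25/54) = 3.52, and power = Φ(5/3.52 − 1.96), about 30%.

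| Insensate share | Pooled difference | Power, whole sample | Power, sensate only |
|---|---|---|---|
| 0% | 10 mm | 80% | 80% |
| 25% | 7.5 mm | 52% | 68% |
| 50% | 5 mm | 30% | 51% |
| 75% | 2.5 mm | 15% | 29% |
| 90% | 1 mm | 8% | 14% |

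Under these assumptions sensory status carries information that the pooled analysis loses. How much depends wholly on a share that the article does not give.

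**5. Chance imbalance.** The SD of the between-arm difference in sensate share is √[2p(1 − p)/54]. That is 0.077 at p = 0.2 and 0.094 at p = 0.6. By normal approximation, a gap of at least 10 points in either direction arises in roughly 19% to 29% of trials. If sensate feet averaged 40 mm (assumed), such a gap would move the pain difference by 0.10 × 40 = 4 mm. Adjustment for sensory status would remove most of that noise.

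**The case against.** The strongest reply is that the floor effect is conjecture. No criterion requires neuropathy and no insensate share is given. The Background calls ulceration multi-factorial and does not describe two exclusive routes. Only pain that prevents debridement is excluded, so lesser pain is admitted, as are infected and deep ulcers. The article itself expects pain: it is a listed reason for ceasing LFUD, and excess pain is a listed possible adverse event. All of this stands. A reader might infer that eligibility makes the sample mainly neuropathic, with scores near zero in most participants. The documents do not support that; they support only an unknown share with reduced sensation.

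A second reply is that the pain model may be in a statistical analysis plan that is not shown. That covers subgroups and interaction terms. It does not fully cover the adjustment set, which the article states for all analyses and justifies by healing alone.

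Third, the whole-sample difference is a legitimate average effect in eligible patients, the article claims no equivalence, and chance imbalance is already reflected in the confidence interval. This is correct. The case for the extra covariates is precision and interpretability, not removal of bias.

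Fourth, a reader might infer that peri-wound scalpel work in LFUD sessions by itself narrows the contrast. Table 2 has that step in both arms, and a shared component does not by itself shrink an additive difference. What remains is that the article does not say which part of the session the during-treatment reading covers.

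**Conclusion.** The point holds as a limited improvement to one secondary outcome. The stated adjustment set was chosen for healing, is applied to pain as well, and leaves out two recorded baseline values that are likelier to predict pain. A null pain result could partly reflect a floor effect, and the article's stated limitation on pain (ulcers lying close together) does not mention loss of sensation.

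The size is not computable from the documents. The sensate shares, the 15 mm and 10 mm differences, the 40 mm mean and the 18.5 mm SD are all assumptions, used only to show the mechanism and its range. Nothing here is a contradiction or a miscalculation, and the primary result does not depend on it.

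**What to change.** - Keep the whole-sample comparison as the main pain analysis. Making a sensate-only comparison the main one is not advised: at a 20% sensate share it would rest on 0.20 × 54, about 11 participants per arm.
- In the pain model, add baseline sensory status and the first-visit pre-treatment VAS as covariates. Name the sensory test and how it is categorised. Do not adjust for each later session's pre-treatment VAS: after the first week it is a post-randomisation value that treatment may have changed. The Randomisation section starts treatment and measurements after allocation, so the first VAS is best recorded before the envelope is opened.
- As supporting results, report pain by sensory status with a group-by-sensation term, and the share of zero scores by arm.
- State that a null whole-sample result will not be read as equal pain.
- Specify that the during-treatment VAS is read at the same point in both arms, while the wound bed is being debrided. This has to be settled before data collection because it cannot be recovered later.

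The cost is a few lines of text, slightly more analysis work and one instruction on VAS timing. The covariates come from assessments already planned. The supporting result by sensory status will have low precision and should be presented as such.

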** *Direct health costs* **			
*Consumable costs for treatments*	*In dollars for each treatment*	*Treating podiatrist*	*Weekly, per participant until healed or at 6 months*
*Medicare Benefit Scheme (MBS)*	*MBS Care database, in dollars*	*Extraction from MBS database*	*End of project for each participant from initial to final treatment*
*Pharmaceutical Benefit Scheme (PBS)*	*PBS Care database, in dollars*	*Extraction from PBS database*	*End of project for each participant from initial to final treatment*
*Inpatient data*	*Monash Health:*	*Hospitalisation costs*	*Monash Health:*
	*Admission duration, reason for admission, imaging and interventions, obtained from the patient record and from the Victorian Admitted Episodes Database*		*End of project*
			*External organisation: End of project*
	*External organisation: Admission duration, reason for admission, costs of any surgery for diabetes-related foot ulcers will be estimated using WEISS funding*		
*Hospital based services (outpatient data)*	*Hours – time spent*	*Treating podiatrist*	*Weekly per participant until healed or at 6 months*
*Medical imaging and pathology for outpatients*	*Dollars – hospital based costs*	*Treating podiatrist*	*Monthly per participant until healed or at 6 months*
*Community based services*	*Number and cost of appointments*	*Participant interview*	*Monthly until healed or at 6 months*
*Private health appointments*	*Number and cost of appointments, eligibility for private health subsidies*	*Participant interview*	*Monthly until healed or at 6 months*
*Royal District Nursing Service for ulcer management*	*Frequency and cost of service*	*Participant interview*	*Monthly until healed or at 6 months*
*Ongoing ulcer care products*	*Valued using market prices*	*Participant interview*	*Monthly until healed or at 6 months*
*Parking costs for appointments*	*Dollars*	*Participant interview*	*Monthly until healed or at 6 months*
*Transportation costs to travel to appointments*	*Estimated through Australian Tax Office car rate cents per km*	*Participant interview*	*Monthly until healed or at 6 months*

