Theatre-based sharps debridement has been utilised for removal of deep necrotic tissue, gangrene and deep infection [14] but has not been routinely used as part of standard care. Non-surgical sharps debridement is required more regularly to remove non-viable necrotic tissue from the ulcer surface and is recommended as part of standard ulcer care [13]. The need for and appropriate method of ulcer debridement should be determined based on the clinical presentation [12] and potentially the clinical skillset and equipment available [13].

Sonoca 185™ (SÖering) was introduced in Australia recently as an alternative method for ulcer debridement. The technology works by delivering low frequency ultrasound, or sound waves, through a constant flow of saline. Ultrasound results when electrical energy is converted to sound waves at frequencies above the range of human hearing (20 kHz) with Sonoca 185™ functioning at 25 kHz [15]. These sound waves can then be transmitted to tissue, via a liquid medium, through a treatment applicator. It is the non-thermal effects of ultrasound that have been shown to cause two phenomena at the ulcer surface; acoustic streaming [15-17] (a steady mechanical force delivered in a fluid medium i.e. sterile saline) and cavitation [15-17] (formation of gas bubbles in the fluid creating micro-shockwaves). The combined effects of acoustic streaming and cavitation are thought to alter cell membrane activity and increase the activity of each cell [16]. Subsequently this is thought to have three clinical effects: debridement, a bactericidal effect and an ulcer healing stimulator effect [17-19].

The biological effects indicated through in vitro and animal studies could contribute to ulcer healing [20]. These effects include stimulation of cellular activity and protein synthesis, the activation of inflammatory cells and the production of chemical mediators that activate fibroblasts and may lead to ulcer healing [15,19,20]. Additionally the mechanical forces produced by the ultrasound energy at the cellular and molecular levels may promote ulcer healing by fostering cell division, angiogenesis, the release of growth factors [20] and stimulating collagen synthesis [15,19]. In vitro data has also found that low frequency ultrasonic debridement (LFUD) is effective in reducing microbe count for methicillin-resistant staphylococcus aureus, vancomycin resistant enterococci, pseudomonas and other commonly occurring bacteria [17,18].

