Non-surgical sharps debridement has been considered the leading comparator to TBSD for several reasons; the technique is simple and requires the use of basic instruments by a trained professional; it is time efficient and can be performed in clinic or at the bed-side; does not require the resources of an operating theatre and has a lower overall cost.

Evidence on the most appropriate method, frequency and extent of DRFU debridement is limited and insufficient to draw any conclusions. The National Evidence-Based Guidelines for the Prevention, Identification and Management of Foot Complications in Diabetes recommends that NSSD should be considered first and should occur repeatedly and as often as required to remove all non-viable tissue [2]. This recommendation is based on expert opinion in the absence of evidence pertaining to DRFU debridement.

A recent Cochrane Review [10] on debridement of diabetic foot ulcers notes that while ulcer debridement is recommended as an effective intervention to assist healing, no guidelines identify a specific method of debridement. The methods of debridement reviewed included surgical debridement, topical hydrogels and larval therapy [10]. Neither NSSD nor LFUD were investigated in the Cochrane Review.

The method of choice for ulcer debridement remains inconclusive. Evidence suggests that each ulcer needs to be individually assessed in terms of type, size, position, appearance, patient pain and tolerance, cost effectiveness and available expertise and equipment to determine the most suitable method of debridement [25].

The decision to utilise NSSD as the active control group in this study was based on the expert opinion in clinical guidelines and the low cost and easy accessibility of the treatment for clinicians. The limited data around LFUD leaves a gap in the evidence that warrants further investigation. The limited data available on LFUD with NSSD as standard practice makes this debridement modality a choice comparator.

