### Economic analysis

#### Cost effectiveness analysis

Direct and indirect health care costs will be collected at regular intervals, as explained in Table 3.

The formula for assessing cost effectiveness analysis will be:

$$\frac{{\mathrm{Cost}}_{\mathrm{LFUD}}–{\mathrm{Cost}}_{\mathrm{NSSD}}}{{\mathrm{Effect}}_{\mathrm{LFUD}}–{\mathrm{Effect}}_{\mathrm{NSSD}}}=\mathrm{Incremental}\;\mathrm{cost}\;\mathrm{per}\;\mathrm{additional}\;\mathrm{ulcer}\;\mathrm{healed}$$

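### Table 4 has no cost line for the ultrasonic device; if costs are taken from it as written, LFUD's cost is understated and both economic ratios shift in its favour

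*Protocol article*

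**What the plan says.** Table 4 of the protocol article (Secondary outcome measures) gives each cost item a measurement tool, a source and a time frame. The direct health costs are treatment consumables, MBS and PBS claims, inpatient data, outpatient hospital services, outpatient imaging and pathology, community services, private appointments, district nursing, ulcer care products, parking and transport. Lost work time is the one productivity cost.

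Two lines concern delivery of the debridement. One is "Consumable costs for treatments* *In dollars for each treatment* *Treating podiatrist". The other, for hospital outpatient services, is measured as "Hours – time spent". The list is detailed enough to include "Parking costs for appointments" and a tax-office rate per kilometre.

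The LFUD device, according to the Background, "was introduced in Australia recently as an alternative method for ulcer debridement". Table 2 shows that a handpiece is used at treatment: "Constantly move the handpiece to prevent ultrasound burning tissue". Of NSSD the Background says "the technique is simple and requires the use of basic instruments by a trained professional", and it gives low cost as one reason for choosing NSSD as the control.

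The Economic analysis section says "Direct and indirect health care costs will be collected at regular intervals" and refers to Table 3 for the details. Table 3 is the ulcer-measurement technique; the cost list is in Table 4. The cost-effectiveness and cost-utility formulas have the same numerator, Cost_LFUD minus Cost_NSSD. The Background states the economic aim as a difference in overall costs between the two methods.

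**The concern.** The arms differ by design in the equipment used to debride. LFUD needs a dedicated device; NSSD needs a scalpel and simple instruments. Table 4 has no line for that difference, although it records much smaller items.

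If the analysts cost only what Table 4 lists, the device enters the comparison at zero. The trial could then report LFUD as cheaper, or as cheaper per ulcer healed, than it would be for a service that has to obtain and maintain the machine. The article says that it wants to inform health services about the financial impact of both treatments, and a service deciding whether to adopt LFUD needs this item.

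**Working it through.** **Step 1: does any existing line cover the device?**

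| Table 4 line | Could it carry the device cost? |
|---|---|
| Treatment consumables, dollars per treatment | Not in the ordinary meaning of the word for a capital item or its servicing. Possibly for handpieces and reprocessing: the term is undefined, and the article does not say whether handpieces are single-use or reusable. |
| Outpatient hospital services, hours | Time only. A uniform overhead-loaded hourly rate applied to both arms would not assign the device to LFUD. |
| MBS, PBS, imaging and pathology | Not described as covering podiatry equipment. |
| Inpatient data | Admission duration, reason, imaging, interventions and surgery. Treatment is expected to be mainly outpatient (Participants and setting). |
| Community, private, nursing, products, parking, transport, work time | No. |

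The device is on no line. The status of handpieces and reprocessing is unclear.

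**Step 2: direction.** Let c be the LFUD-only cost per participant that is left out, net of any comparable NSSD instrument cost.

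- Recorded numerator = (Cost_LFUD − c) − Cost_NSSD = true numerator − c.
- Shift in either ratio = −c / (effect difference).

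With c above zero and a positive effect difference, both ratios come out too low. With a negative effect difference, the numerator is still too low by c, so LFUD looks less costly, or more cost-saving, than it is. In both cases the error favours LFUD.

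**Step 3: size.** The plan states no unit cost, device price or expected ratio, so there is no figure to reproduce. The sensitivity per omitted dollar can be shown.

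Inputs from the article:
- Healing proportions 0.25 and 0.41, difference 0.16 (Sample size).
- 3 ulcers per participant (Sample size), so 0.16 × 3 = 0.48 extra ulcers healed per participant.
- Weekly treatment for six months (Abstract, Methods), about 26 sessions.
- Review of LFUD after six weeks, with a possible change to NSSD (Primary outcome measure), about 6 sessions for a participant who changes then.

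Shift in cost per additional ulcer healed, for $1 omitted per session:
- 6 sessions: 6 / 0.48 = $12.5
- 26 sessions: 26 / 0.48 = $54.2

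The shift is proportional to the omitted amount. At assumed values of $5 and $50 per session over 26 sessions:
- $5: 130 / 0.48 = $271
- $50: 1,300 / 0.48 = $2,708

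For the cost-utility ratio the article gives no expected QALY gain. With assumed gains of 0.01 and 0.05, $1 omitted per session over 26 sessions shifts the ratio by 26 / 0.01 = $2,600 and 26 / 0.05 = $520.

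The omitted amount per session is the yearly equipment cost divided by the number of sessions per year on the machine. It halves if the machine is used twice as often, so use outside the trial matters as much as the price.

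**The case against.** The strongest reply is that silence is not exclusion. Table 4 summarises outcome measures and when they are collected, and nearly every row has a participant-level or database source. A device price is a one-off institutional figure, applied when resources are valued, and a condensed article may leave valuation rules to a fuller costing plan. The article does not even say how hours become dollars. This part stands: the documents do not show that the final ratios will be biased, only that they would be if costs are taken from Table 4 as written. The reply does not remove the point, because the article does fix an itemised cost list, and that list lacks the item on which the arms differ by design.

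A reader might also infer that handpieces and their reprocessing are excluded. The documents do not support that; they may be booked as "Consumable costs for treatments".

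A reader might put a dollar figure on the bias from a guessed purchase price, a guessed life and use by trial participants alone. None of these is in the documents, and charging the machine only to the trial would inflate the result if the department also uses it for other patients.

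The sentence on basic instruments explains the advantage of NSSD over theatre-based debridement, not over LFUD. It describes what NSSD requires, but is not itself a cost comparison of the two trial arms.

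Finally, the matter is limited to a secondary outcome. The healing comparison and the sample size are untouched, and the cost could still be added at analysis from hospital records.

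**Conclusion.** The concern holds in conditional form. Table 4 names no purchase, lease, depreciation or maintenance cost for the LFUD device, and leaves open whether handpieces and reprocessing are consumables. Followed as written, it understates Cost_LFUD, shifts both ratios in favour of LFUD, and does not deliver the comparison of overall costs that the article sets as an aim.

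The direction rests only on the net omitted equipment cost being higher for LFUD. The size cannot be determined from the documents. The illustration, about $12.5 to $54 per additional ulcer healed for each $1 omitted per session, rests on the planned 0.16 difference, 3 ulcers per participant and 6 to 26 LFUD sessions. The true effect may be small if the machine is shared widely and lasts long.

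This should be corrected, as it concerns one of the stated aims and is cheap to repair, but it does not threaten the primary result.

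**What to change.** 1. Add an equipment line to Table 4 for both arms: for LFUD, the generator, its maintenance, and any reusable handpieces with their sterilisation; for NSSD, reusable instruments and their sterilisation. Value it as an annuitised cost per treatment from hospital purchase, service and sterilisation records, and include it in both ratios.
2. Define consumables, and say where handpieces and reprocessing are booked, so that nothing is omitted or counted twice.
3. Vary equipment life and yearly throughput in a sensitivity analysis, including use of the machine outside the trial.
4. In the cost-effectiveness paragraph, change the cross-reference for cost collection from Table 3 to Table 4.

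The cost is a little more costing work, with no additional visits or participant data and no change to treatment. LFUD's cost result will become less favourable by whatever the equipment adds.
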